#### Economic analysis

The trial-based health economic analysis will consider two questions:

How cost-effective is a) an Active approach to case-finding and b) a simple Opportunistic approach compared with routine detection of COPD (routine care), in terms of cost per additional case detected?

A within-trial patient level analysis will be undertaken to determine the total and mean costs of case finding for each trial arm. An incremental cost-effectiveness analysis from a health care perspective will determine the cost per additional case detected, with a sensitivity analysis taking into account patient out of pocket costs in addition to health care costs. True cases of COPD detected by each method will be determined within the trial. The cost of case finding and spirometry will be established within the trial, and resource use data will be collected for each method and will include staff time, equipment, diagnostic testing and any consumables required. Data will be collected from a representative sample of practices to ensure generalisability. Unit costs (e.g. staff costs, equipment) will be collected from published sources. In addition a patient cost questionnaire will be administered to all who attend for spirometry to determine their out of pocket (travel and time) costs.

By using data from the trial which uses West Midlands’ practices only, there may be limits to the generalisability of the results of the trial. This will be explored within the economic evaluation using extensive sensitivity analysis. Key parameters will be varied to determine the impact of changes on results. Case finding in different patient sub-groups will also be considered. Non-parametric bootstrapping and probabilistic sensitivity analysis will be undertaken to explore uncertainty in the confidence to be placed on the results of the economic analysis and cost effectiveness acceptability curves presented.

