**Methods/Design:**

In this study, using a cluster randomised controlled trial (RCT) in 56 general practices in the West Midlands, we plan to investigate the effectiveness and cost-effectiveness of a Targeted approach to case finding for COPD compared with routine practice. Using an individual patient RCT nested in the Targeted arm, we plan also to compare the effectiveness and cost-effectiveness of Active case finding using a postal questionnaire (with supplementary opportunistic questionnaires), and Opportunistic-only case finding during routine surgery consultations.

All ever-smoking patients aged 40-79 years, without a current diagnosis of COPD and registered with participating practices will be eligible. Patients in the Targeted arm who report positive respiratory symptoms (chronic cough or phlegm, wheeze or dyspnoea) using a brief questionnaire will be invited for further spirometric assessment to ascertain whether they have COPD or not. Post-bronchodilator spirometry will be conducted to ATS standards using an Easy One spirometer by trained research assistants.

The primary outcomes will be new cases of COPD and cost per new case identified, comparing targeted case finding with routine care, and two types of targeted case finding (active *versus* opportunistic). A multilevel logistic regression model will be used to model the probability of detecting a new case of COPD for each treatment arm, with clustering of patients (by practice and household) accounted for using a multi-level structure.

A trial-based analysis will be undertaken using costs and outcomes collected during the trial. Secondary outcomes include the feasibility, efficiency, long-term cost-effectiveness, patient and primary care staff views of each approach.

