## Methods

### Aims and objectives

To determine whether Targeted case finding is more effective and cost-effective than routine practice.To evaluate the relative effectiveness and cost-effectiveness of two alternative methods of targeted case finding: Active (postal questionnaire plus flagging of patient records) versus Opportunistic (flagging only).

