### Outcomes

#### Primary outcomes

The primary outcomes are the percentage of the eligible population diagnosed as new COPD cases within the first year, and cost per additional case identified in each arm, comparing:Targeted case finding and routine practiceActive and opportunistic case finding

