#### (a) Targeted case finding versus Routine care cluster randomized design

Based on the authors’ modelling work [32], the proportion of new COPD cases detected in the Targeted group (averaged across both Active and Opportunistic arms) was assumed to be 3.15%. Based research by Simpson et al. [42], the proportion of new COPD cases detected in the Routine care group was assumed to be 0.75%. At the 4.75% significance level, with 80% power, this led to an unadjusted sample size required of 545 per group, in order to detect a difference of 2.4% between Targeted and Routine care arms.

We expect ~40% of a practice population to be age 40-79 yrs with 57% of these being ever smokers without a previous diagnosis of COPD [32]. Assuming therefore a conservative 1000 eligible patients per practice of average list size 6000, and adjusting for clustering of patients within practices, assuming a conservative ICC of 0.05 [43, 44] the sample size required was 27,768 per arm, equivalent to 28 practices per arm.

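### The two questions posed in the economic analysis (Active v Routine, Opportunistic v Routine) do not match the two primary cost contrasts (Targeted v Routine, Active v Opportunistic)

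*Protocol article*

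**What the plan says.** Three places in the article agree on the cost contrasts.

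- **Primary outcomes** lists "cost per additional case identified in each arm, comparing:Targeted case finding and routine practiceActive and opportunistic case finding".
- **Abstract, Methods/Design** has the same pair for new cases and cost per new case: "comparing targeted case finding with routine care, and two types of targeted case finding (active *versus* opportunistic".
- **Aims and objectives** makes Targeted against routine practice the first aim. The second begins "To evaluate the relative effectiveness and cost-effectiveness of two alternative methods of targeted case finding", that is, Active against Opportunistic.

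The **Economic analysis** section then states: "The trial-based health economic analysis will consider two questions". What follows is "How cost-effective is a) an Active approach to case-finding and b) a simple Opportunistic approach compared with routine detection of COPD (routine care", measured as cost per additional case detected. Both parts have routine care as comparator.

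The same section promises to "determine the total and mean costs of case finding for each trial arm" and adds: "An incremental cost-effectiveness analysis from a health care perspective will determine the cost per additional case detected". That second sentence does not say which arms the increments are taken between. Bootstrapping, probabilistic sensitivity analysis and acceptability curves are also promised, again without being tied to a contrast.

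The effectiveness sections do follow the primary outcomes. Primary analyses covers Targeted v Routine and Active v Opportunistic. Each component of the Targeted arm against Routine appears only under Secondary analyses.

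**The concern.** The economic section does not leave its comparators to a fuller document. It counts its questions, names the comparator, and arrives at a different pair from the one declared primary. Comparisons that are secondary for effectiveness become the leading questions for cost.

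This matters most for the second aim. Routine, Opportunistic and Active are alternatives of which a practice would adopt one. A commissioner already prepared to pay for Opportunistic case finding needs the extra cost per extra case of adding the postal questionnaire. A ratio of Active against Routine averages that step with the step from Routine to Opportunistic, so it answers a different question. Someone working from the stated questions alone could finish the economic analysis without reporting a declared primary outcome.

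**Working it through.** **1. Reproduce the planned yields** (inputs from the sample size section, part b).

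- Active: (0.50 + 0.50 × 0.91 × 0.50 × 0.90) × 0.48 × 0.70 × 0.17 = 4.026%; × 19,152 = 771 cases, as stated.
- Opportunistic: 0.91 × 0.50 × 0.90 × 0.48 × 0.70 × 0.17 = 2.339%; × 19,152 = 448 cases, as stated. (The 91% who visit the GP is needed to reach 448, although the text mentions it only for the Active arm.)
- Targeted: part (a) says "the proportion of new COPD cases detected in the Targeted group (averaged across both Active and Opportunistic arms) was assumed to be 3.15" per cent, which is (2.3 + 4.0)/2.
- Routine: 0.75%, from part (a).

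**2. Additional cases per eligible patient**, using the rounded yields.

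| Contrast | Difference in yield |
|---|---|
| Opportunistic v Routine (O v R) | 2.30 − 0.75 = 1.55 points |
| Active v Routine (A v R) | 4.00 − 0.75 = 3.25 points |
| Targeted v Routine (T v R) | 3.15 − 0.75 = 2.40 points |
| Active v Opportunistic (A v O) | 4.00 − 2.30 = 1.70 points |

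**3. How the ratios relate.** Let c_O and c_A be the mean extra cost per eligible patient over Routine.

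- O v R = c_O/0.0155
- A v R = c_A/0.0325
- T v R = ((c_O + c_A)/2)/0.0240, the two sub-arms being of equal size
- A v O = (c_A − c_O)/0.0170

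Since 3.25 = 1.55 + 1.70, A v R is a weighted average of O v R and A v O, with weights 1.55/3.25 = 0.48 and 1.70/3.25 = 0.52. It therefore lies between them and equals A v O only when all the ratios are equal. That happens at c_A/c_O = 3.25/1.55 = 2.10 (2.06 with unrounded yields).

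**4. Illustration.** The documents contain no unit costs. Those below are hypothetical: c_O = £2, c_A from £3 to £6. Results are £ per additional case.

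| c_A | O v R | A v R | T v R | A v O |
|---|---|---|---|---|
| £3 | 129 | 92 | 104 | 59 |
| £4 | 129 | 123 | 125 | 118 |
| £5 | 129 | 154 | 146 | 176 |
| £6 | 129 | 185 | 167 | 235 |

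**5. Reading the table.** At c_A = £5, a payer willing to spend £160 per case would accept Active on A v R (£154) but not on A v O (£176). A payer willing to spend £200 would be wrong to choose Opportunistic merely because £129 is the lowest ratio against Routine, since the step to Active costs £176. Below a cost ratio of 2.10, Active has both the higher yield and the lower ratio against Routine. Opportunistic is then extendedly dominated, and the two ratios against Routine already show this.

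**The case against.** The strongest reply is that nothing is withdrawn. The Primary outcomes section still stands, and the economic section commits to patient-level costs for each arm, cases by method, and an incremental analysis not confined to Routine. Active v Opportunistic follows by subtraction and Targeted v Routine by pooling two equal sub-arms. This stands. A reader might infer that the economic analysis will deliver neither primary contrast; the documents do not support that.

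A reader might also infer that the comparison randomised within practice is given up. It is not. The primary analysis within the targeted group estimates that risk difference and the number needed to target directly, and patient-level costs keep the cost side available. What subtraction of arm means does not supply is the uncertainty: an interval or acceptability curve for Active v Opportunistic cannot be read from two separate comparisons with Routine.

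Third, any claim that the plan points to the wrong strategy rests on costs the documents do not give and on readers stopping at ratios against Routine. This also stands. The direction of the difference reverses at a cost ratio of about 2.1, and below it the ratios against Routine rank the options correctly.

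Fourth, each deliverable strategy against routine care is a sensible question, and Targeted is a trial mixture of two strategies rather than an option to adopt. True, but the article itself chose Targeted v Routine as primary.

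Finally, rules for dominance belong in a health-economic plan, so their absence is no fault here. Lists also run together in the available text, so reading a) and b) as the two announced questions is the natural reading but not a certain one.

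**Conclusion.** The mismatch is real and concerns a declared primary outcome. Three sections name Targeted v Routine and Active v Opportunistic; the section that sets out the analysis names two other contrasts and never poses Active v Opportunistic. It is a contradiction in what is stated, not a detail left out by condensation.

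The consequence is limited to a risk of incomplete or misdirected reporting, since the data needed for both contrasts are planned. Its size cannot be fixed from the documents. Over the hypothetical range above, Active v Routine runs from £33 above Active v Opportunistic (92 − 59) to £50 below it (235 − 185). Those amounts illustrate and do not predict. The finding that the two differ unless the cost ratio is about 2.1 rests only on the planned yields. It is worth correcting before the economic analysis is done, but it does not undermine the design.

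**What to change.** Reword the opening of the Economic analysis section so that:

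1. the primary economic comparisons are Targeted v Routine and Active v Opportunistic, as in Primary outcomes, each with bootstrapped uncertainty and an acceptability curve;
2. a fully incremental comparison of Routine, Opportunistic and Active is reported, with options ordered by cost and dominated or extendedly dominated options identified;
3. Active v Routine and Opportunistic v Routine are labelled secondary, as Secondary analyses already does for effectiveness.

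The cost is a few sentences and some extra output from the same patient-level costs and outcomes. No new data collection or change to sample size is needed.

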### Statistical justification for sample size

As there are two primary outcomes, the significance level for multiple testing is adjusted so that in total (across both sample size calculations) there is a 5% significance level. The individually randomised component (outcome (b) below) comparing Active versus Opportunistic case finding requires far fewer patients for adequate power and is therefore given 0.25% significance level. The cluster component (a) is designated 4.75% significance level.

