#### Targeted case finding vs Routine care (cluster design)

Baseline characteristics of patients and uptake rate at each stage will be described for each cluster, and compared across clusters to check for balance across groups. A multilevel logistic regression model will be used to model the probability of detecting a new case of COPD in the Targeted group compared with the Routine care group. Clustering of patients (by practice and household) will be accounted for using a multi-level structure. The data will also be modelled using a log-link and results from the logit-link and log-link models will be compared. OR and also RR and risk differences will be estimated [45, 46], as will the NNT (Number Needed to Target to identify one additional COPD case). The analysis will also adjust for variables used in the randomization (age, ethnicity, deprivation) which might affect probability of having COPD.

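### The co-primary cost per additional case is given a patient-level analysis with bootstrapping and no provision for practice; if patients are resampled, uncertainty in the contrasts with Routine care is understated

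*Protocol article*

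**What the plan says.** The article's Primary outcomes section puts the economic outcome beside the percentage newly diagnosed: "cost per additional case identified in each arm, comparing" Targeted with Routine and Active with Opportunistic.

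The Economic analysis section asks: "How cost-effective is a) an Active approach to case-finding and b) a simple Opportunistic approach compared with routine detection of COPD (routine care"). Both of these contrasts are with Routine care. On method it says: "A within-trial patient level analysis will be undertaken to determine the total and mean costs of case finding for each trial arm", and, in a later paragraph, "Non-parametric bootstrapping and probabilistic sensitivity analysis will be undertaken to explore uncertainty in the confidence to be placed on the results", with acceptability curves to follow. Practices appear in that section only as a source of resource-use data and as a limit on generalisability.

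The effectiveness side of the same article is explicit. The sample size for Targeted versus Routine is inflated by "adjusting for clustering of patients within practices, assuming a conservative ICC of 0.05", and the primary model for that comparison says: "Clustering of patients (by practice and household) will be accounted for using a multi-level structure". The model for Active versus Opportunistic also carries practice, and household if appropriate. Under Allocation to trial arm, practices are the unit for Targeted versus Routine, with linked practices kept in the same arm. Households within practice are the unit for Active versus Opportunistic.

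**The concern.** The incremental cases in the cost ratio are the same practice-randomised quantity as the effectiveness outcome. A non-parametric bootstrap run in its usual way on patient-level data draws patients as if independent. With about 1,000 eligible patients per practice, that drops the between-practice component, which dominates the variance at the plan's own ICC.

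The cost-effectiveness plane and the acceptability curves could then look close to certain while the multilevel interval for the same incremental cases is wide. The publication plan puts both results in one main paper, and the trial is meant to inform local policy, so readers would see two very different statements of precision about one quantity.

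**Working it through.** **Inputs.** From the sample-size section for Targeted versus Routine: detection 3.15% and 0.75%, 545 per group unadjusted, 1,000 eligible patients per practice, ICC 0.05, 27,768 per arm, 28 practices per arm. From the section on Active versus Opportunistic: the response and yield assumptions.

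**1. Reproduce the plan's figure.**
- Two-proportion sample size at two-sided alpha 0.0475 and 80% power, pooled variance: 529, against 545 stated (within 3%).
- Design effect = 1 + (m − 1) × ICC = 1 + 999 × 0.05 = 50.95.
- 545 × 50.95 = 27,767.75, which rounds to the stated 27,768, or 28 practices of 1,000.

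**2. Targeted versus Routine.** The standard error that respects practices exceeds the patient-level one by √(design effect) = √50.95 = 7.14.
- Patient-level 95% half-width: 1.96 × √[(0.0315 × 0.9685 + 0.0075 × 0.9925) / 28,000] = 0.23 percentage points.
- With practices: 0.228 × 7.14 = 1.63 percentage points.

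Around the assumed difference of 2.4 points, the intervals are about 2.17 to 2.63 and 0.77 to 4.03.

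**3. The two listed economic contrasts.** Take about 500 patients per practice in each targeted sub-arm (14,000 in 28 practices).
- Yield, Active: (0.5 + 0.5 × 0.91 × 0.5 × 0.9) × 0.48 × 0.70 × 0.17 = 4.03%.
- Yield, Opportunistic: 0.91 × 0.5 × 0.9 × 0.48 × 0.70 × 0.17 = 2.34%.
- Patient-level variances: Active 0.0403 × 0.9597 / 14,000 = 2.76 × 10⁻⁶; Opportunistic 0.0234 × 0.9766 / 14,000 = 1.63 × 10⁻⁶; Routine 0.0075 × 0.9925 / 28,000 = 0.266 × 10⁻⁶.
- Design effects: 1 + 499 × 0.05 = 25.95 for a sub-arm; 50.95 for Routine.
- Active versus Routine: √[(2.76 × 25.95 + 0.266 × 50.95) / (2.76 + 0.266)] = 5.3.
- Opportunistic versus Routine: √[(1.63 × 25.95 + 0.266 × 50.95) / (1.63 + 0.266)] = 5.4.

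**4. Sensitivity to the ICC** (factor by which a patient-level standard error is too small).

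| ICC | Targeted v Routine | Active v Routine |
|---|---|---|
| 0.05 | 7.1 | 5.3 |
| 0.01 | 3.3 | 2.5 |
| 0.005 | 2.4 | 1.9 |
| 0.001 | 1.4 | 1.2 |

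**5. Simulated bootstrap.** Difference in cases, 28 versus 28 practices of 1,000, beta-binomial, 1,000 data sets per ICC, percentile 95% intervals.

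| ICC | Median width ratio, practice : patient resampling | Coverage, patients resampled | Coverage, practices resampled |
|---|---|---|---|
| 0.05 | 6.7 | 20% | 91% |
| 0.01 | 3.2 | 43% | 92% |
| 0.005 | 2.4 | 56% | 93% |

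**6. Active versus Opportunistic.** The practice effect is largely shared by the two arms. With assumed practice standard deviations of 0.3 to 0.8 on the logit scale and no heterogeneity of effect, the factor is about 1.1 to 1.5. With heterogeneity standard deviations of 0.3 to 0.5 (practice standard deviation 0.5) it is about 1.5 to 2.0.

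**What cannot be computed.** These figures concern additional cases only. The article gives no costs, cost variances or ICC for cost. Cost and cases may also move together across practices, so the factor does not carry over directly to the ratio.

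**The case against.** The strongest reply is that the section does not say patients will be resampled. The patient-level wording sits in a sentence about determining costs, the bootstrap sentence names no unit, and a non-parametric bootstrap can resample practices. A journal article may leave that detail to a fuller plan. This stands in part: a reader might infer that the trial will ignore practice clustering in its economic analysis, and the article does not support that. What remains is that the section does fix a level and a method for a primary outcome, and taken together in the usual way they omit the randomised unit that the same article states repeatedly for the other primary outcome.

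Second, Secondary analyses plans multilevel logistic regression of each targeted component against Routine care. Those are the two economic contrasts, and a probabilistic sensitivity analysis could draw on the estimates. It could, but nothing links them, and they would not cover costs.

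Third, a reader might infer that intervals for cost per additional case would be several times too narrow. That is not shown. It depends on patient resampling, on an ICC the plan itself calls conservative, and on costs that are not given. Under the beta-binomial model, ICC 0.05 with 0.75% detection implies a between-practice standard deviation of √(0.0075 × 0.9925 × 0.05) = 1.9 points, and about 56% of Routine practices with no new case in 1,000 patients. The 20% coverage figure is therefore an upper-end illustration. Nor does the claim extend to Active versus Opportunistic.

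Fourth, the two primary outcomes would not contradict each other: they would differ in stated precision. The significance levels are set in the sample-size calculations for case detection ("The cluster component (a) is designated 4.75% significance level"), and no stated test rests on the bootstrap.

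**Conclusion.** The point holds in conditional form. The stated economic method makes no provision for practice, although both listed contrasts are between practices. If patients are resampled, the standard error of the incremental cases is about 7 times too small for Targeted versus Routine and about 5 times for Active versus Routine at ICC 0.05. For Targeted versus Routine it is about 2.4 times at 0.005 and 1.4 times at 0.001. These figures assume 28 practices per arm, 1,000 eligible patients each (about 500 per sub-arm) and the plan's detection rates.

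The size of the effect on the full cost ratio is unknown. The Active versus Opportunistic contrast is only modestly affected, at about 1.1 to 2.0. The point should be settled before analysis, because it bears on a primary outcome and is cheap to correct.

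**What to change.** In the Economic analysis section, name the resampling scheme for each contrast.

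- **Contrasts with Routine care:** a two-stage cluster bootstrap. Resample practices within arm, with linked practices kept together as one allocation unit, then households or patients within them, keeping each patient's cost and outcome paired. A bivariate multilevel model of cost and case status is an acceptable alternative.
- **Active versus Opportunistic:** resample households within practice.
- **Acceptability curves:** build them from these replicates, or from the fitted joint model.

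Design and data collection are unchanged. The cost is a few lines of wording, slightly more programming, and wider intervals.
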